## Abstract

**Background:**

Electroacupuncture has been used for treatment in patients with overactive bladder. This study was conducted to evaluate the efficacy and safety of electroacupuncture for treating overactive bladder of postmenopausal women.

**Methods/design:**

This is a multicenter, randomized controlled, parallel clinical trial. Two hundred ninety participants with overactive bladder syndrome will be recruited from Dongguk University Bundang Oriental Hospital and Cheonan Korean Medicine Hospital of Daejeon University and randomly allocated into one of two groups in a 1:1 ratio. One group will receive electroacupuncture (EA) and the other acupuncture (AC). The allocation will be concealed from both participants and assessors. The study period will be about 10 weeks, including 6 weeks of electroacupuncture or acupuncture treatment and a four week follow-up period. Both EA group and AT group will undergo acupuncture at 7 fixed points, and the EA group will undergo electronic stimulation at 6 points. The primary outcome will be the average number of micturitions per 24 h based on a 3-day bladder diary. The secondary outcome will comprise the 3-day bladder diary, the overactive bladder symptom score and the results of the King’s health questionnaire.

**Discussion:**

The results of this trial will provide information regarding the efficacy and safety of electroacupuncture for treating overactive bladder in postmenopausal women.

**Trial registration:**

ClinicalTrials.gov, NCT03260907. Registered on 24 August 2017.

**Electronic supplementary material:**

The online version of this article (10.1186/s13063-018-2715-3) contains supplementary material, which is available to authorized users.

## Background

Overactive bladder (OAB) is a highly prevalent disorder that has a negative impact on quality of life [1, 2]. OAB is defined as urinary urgency, usually accompanied by frequency and nocturia, with or without urgent urinary incontinence, in the absence of urinary tract infection (UTI) or other obvious pathology [3–5]. In patients with OAB, frequency (85%) is the most commonly reported symptom, followed by urgency (54%) and urge incontinence (36%) [6].

The condition is more common in women and in people over 40 years of age [2, 3]. The prevalence of OAB increases with age and duration of menopause [6]. The overall prevalence of OAB in Korean women has been shown to be 14.3%, while it was 18.4% for those aged over 40 [7, 8].

Acupuncture, which is one of the primary treatments utilized traditional Korean medicine (TKM), involves various stimulation methods such as electrical devices, moxibustion, pharmacopuncture, and thread-embedding therapy to stimulate acupoints, for controlling bladder function at the lower abdomen and lumbar-sacral area [8]. Among these methods, electroacupuncture is a typical and common treatment for OAB in TKM, which is effective at suppressing excessive contractions and activities of the detrusor muscle, improving bladder compliance, maintaining normal urination, and improving pathological changes in bladder tissue [9, 10]. Mechanical stimulation is supposed to send signals to the spinal cord via the sensory ganglia and interneurons, thereby regulating the activity of motor neurons in the brain stem that control autonomic functions, including urinary activity [11, 12]. However, the efficacy and safety of electroacupuncture are still controversial.

Recent clinical studies have evaluated the efficacy electric stimulation for treating OAB [13] However, a randomized controlled trial (RCT) for validation of the comparative efficacy and safety of acupuncture with electric stimulation as concurrent treatment has not yet been undertaken.

This study will evaluate the efficacy and safety of electroacupuncture for treating OAB of menopausal women.

## Methods/design

### Study design

This is a multicenter, randomized controlled, parallel clinical trial. The study protocol conforms to the Consolidated Standards of Reporting Trials (CONSORT) [14] and Standards for Reporting Interventions in Clinical Trials of Acupuncture (STRICTA) [15] guidelines. The study process is illustrated in Fig. 1. The institutional review board of Dongguk University Bundang Oriental Medical Hospital approved the study (2017–0008). The protocol has been registered in ClinicalTrial.gov (NCT03260907).

**Fig. 1 Fig1:**
[figure not shown]
Flowchart of the study process

Participants will be recruited through advertisements in outdoor areas as well as on hospital websites. Two hundred ninety participants with overactive bladder syndrome will be randomly allocated to one of two in a 1:1 ratio. One group will be the electroacupuncture (EA) group, and the other will be the acupuncture (AC) group. The study period will be about 10 weeks, including 6 weeks of electroacupuncture or acupuncture treatment and a 4 week follow-up period. The schedules for enrollment, intervention, and assessments is shown in Table 1. The SPIRIT checklist is provided in Additional file 1.

**Table 1 Tab1:** Schedule to be used for enrolment, intervention, and assessments. OABSS, overactive bladder symptom score; KHQ, King’s health questionnaire

	Study period													
	Screening	Treatment												Follow-up
Week	0	1		2		3		4		5		6		10
Visit	1	2	3	4	5	6	7	8	9	10	11	12	13	14
Enrollment:														
Informed consent	X													
Demographic characteristics	X													
Medical history	X													
Vital signs	X	X	X	X	X	X	X	X	X	X	X	X	X	X
Physical examination	X												X	
Urinalysis	X												X	
Inclusion/Exclusion criteria	X													
Random allocation		X												
Intervention:														
Acupuncture treatment		X	X	X	X	X	X	X	X	X	X	X	X	
Assessments:														
3-day bladder diary		X											X	X
OABSS	X												X	X
KHQ	X												X	X
Adverse events		X	X	X	X	X	X	X	X	X	X	X	X	X

### Eligibility criteria

Two hundred ninety patients with OAB will be recruited from two hospitals in Korea: Dongguk University Bundang Oriental Hospital in Bundang, and Cheonan Korean Medicine Hospital of Daejeon University in Cheonan. After obtaining informed consent from the patients or their representatives, we will screen them according to the eligibility criteria for enrollment in the study.

### Inclusion criteria

The inclusion criteria for the study will be as follows: (1) women over 40 years of age without the possibility of pregnancy; (2) those who have a history of amenorrhea for at least 1 year and have no previous history of hormone replacement therapy for the last 6 months; (3) those who have symptoms of urinary frequency and urgency lasting more than 3 months; (4) those who fit the diagnostic criteria for OAB, with a total score of more than 3 points on the Korean version of the Overactive Bladder Symptom Score (OABSS); (5) those who have an average urinary frequency of more than eight times per day and urgency defined by the urgency rating scale (URS) on the bladder diary of more than 2 points and/or urgent urinary incontinence (UUI) on the 3-day bladder diary during a 1-week screening period; (6) those who agree to this clinical study after sufficient explanation.

### Exclusion criteria

The exclusion criteria for the study are as follows: (1) diagnosed with UTI by urine examination; (2) having stress urinary incontinence without symptoms of OAB; (3) suspected of having voiding dysfunction induced by neurological damage; (4) a medical history of cystocele, uterine prolapse or similar condition; (5) a medical history of obstructive uropathy such as urinary stones and urinary tumors; (6) a surgical history of urethra or bladder; (7) a medical history of malignant tumors of the urinary tract; (8) a medical history of neurological disease or psychiatric illness; (9) an artificial cardiac pacemaker or implantable cardioverter defibrillator in the chest; (10) having experienced a hypersensitivity reaction after an acupuncture treatment, or showing any other contraindications; (11) having participated in another clinical trial within the past three months; (12) having taken therapeutic drugs that may affect bladder function within one month of the start of this study; (13) having inadequate literacy to complete the study documents.

### Dropout criteria

Patients will be removed from the study if they are unwilling to continue their participation in the study. Patients who fail or anticipate that they might fail to attend at least 10 sessions will also be dropped from the study.

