### Prohibited and permitted concomitant treatment

Participants will be prohibited from receiving any OAB treatment outside of the interventions of this trial during the 6-week treatment period. If a patient start medication for OAB during the treatment period, they will be withdrawn from the trial. All new treatments started after the beginning of the trial and concomitant medications to treat medical conditions unrelated to OAB will be recorded on the Case Report Form (CRF).

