### Statistical analysis

We will analyze results primarily based on the principle of intention-to-treat (ITT) and subordinately based on the per-protocol (PP) principle. The ITT analysis will include any participants who are randomly allocated and have at least one EA or AC session. The PP analysis will cover only patients who have completed at least 10 sessions of EA or AC treatments with no use of medication or medical device of UTI or OAB, and have no serious violation. The primary and secondary continuous outcomes will be compared between randomized groups using ANCOVA models that includes baseline measurement as covariates.

The categorical variables will be analyzed by the Pearson χ^2^ test or Fisher’s exact test. If there is a significant difference between groups in terms of baseline characteristics, analysis of covariance (ANCOVA) or logistic regression for further evaluation will be performed. When it is necessary to control important variables that may affect the final evaluation, stratification analysis (Cochran-Mantel-Haenszel method, etc.) will be applied.

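### The removal rules largely overlap the per-protocol exclusions and, as written, end follow-up before the week-6 primary diary, leaving the ITT set without outcomes for the women removed

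*Protocol article*

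**What the plan says.** Three parts of the Protocol article bear on this.

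- **Leaving the study.** Dropout criteria has two rules: "Patients will be removed from the study if they are unwilling to continue their participation in the study", and "Patients who fail or anticipate that they might fail to attend at least 10 sessions will also be dropped from the study". Prohibited and permitted concomitant treatment adds a third: "If a patient start medication for OAB during the treatment period, they will be withdrawn from the trial". All three speak of the study or the trial, not of trial treatment alone.
- **Analysis sets.** Statistical analysis makes ITT primary: "We will analyze results primarily based on the principle of intention-to-treat (ITT) and subordinately based on the per-protocol (PP) principle". The ITT set is defined thus: "The ITT analysis will include any participants who are randomly allocated and have at least one EA or AC session". The PP set is limited to "patients who have completed at least 10 sessions of EA or AC treatments with no use of medication or medical device of UTI or OAB". Women with a serious violation are excluded from it too.
- **Timing.** Under Primary outcome, the endpoint is the diary at week 6. Table 1 puts that at visit 13, which is also the last of the 12 sessions. The only other diaries are at visit 2 and week 10. The article does not say that women who are removed are still assessed.

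**The concern.** An ITT analysis protects the randomised comparison only if outcomes are sought from women who stop or change treatment. Here, two of the main reasons for being outside the PP set (fewer than 10 sessions, OAB medication) are also reasons for leaving the study. If leaving ends diary collection, ITT and PP are computed on nearly the same women, and neither can serve as a check on the other.

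Removal happens after randomisation and could depend on response and on arm. Starting OAB medication is plausibly a sign of poor response. The practitioner opens the envelope and is unblinded (Randomization, allocation concealment and blinding). On participants the article contradicts itself: the Abstract says allocation is concealed from them, while Outcomes says they cannot be blinded. These statements must be reconciled, because knowledge of the arm affects how far leaving could differ between arms.

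**Working it through.** **1. Overlap of the rules**

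| Ground | Leaves the study? | Outside PP? |
|---|---|---|
| Fewer than 10 of 12 sessions | Yes | Yes |
| OAB medication during the 6 treatment weeks | Yes | Yes |
| Woman anticipates missing the 10-session minimum | Yes | Only if she does miss it |
| Unwilling to continue | Yes | Only if a PP condition fails |
| UTI medication; medical device for UTI or OAB | No rule stated | Yes |
| Serious violation | No rule stated | Yes |

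The overlap is large but not complete, in either direction.

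**2. What is observed.** With diaries only at baseline, week 6 and week 10, a woman removed before week 6 contributes a baseline value and nothing later. There is no interim diary, so any imputation of her primary outcome would rest mainly on baseline data.

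**3. The plan's own drop-out figure.** Under Sample size, 116 / (1 - 0.20) = 145 per group, 290 in total. This reproduces. The planned loss is 0.20 x 145 = 29 per group, or 58 women. (The 116 is slightly more than the 109 to 110 that 0.8, SD 2.1, two-sided 5% and 80% power give. That is conservative and does not affect this point.)

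**4. Possible bias, route A.** Assumptions: SD 2.1 (from the plan), 20% removed in each arm, removal correlated rho with poor response in one arm and unrelated to it in the other.

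- Shift of the retained mean = rho x 2.1 x phi(0.8416) / 0.8 = rho x 2.1 x 0.280 / 0.8 = rho x 0.735.
- rho = 0.3: 0.22, and 0.22 / 0.8 = 28% of the planned effect.
- rho = 0.5: 0.37, and 0.37 / 0.8 = 46%.
- Standard error with 116 per arm = 2.1 x sqrt(2/116) = 0.276. The false-positive rate under no true effect is then about 13% and 27%. A simulation of 2000 runs with 145 per arm gave 12.6% and 27.0%.
- If the selection favours the other arm, power at a true 0.8 falls to about 56% and 36% in the same simulation.

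**5. Possible bias, route B.** Let s be the share removed in an arm, and g the amount by which removed women do worse than retained women. The retained mean is better than the full mean by s x g, so the bias in favour of EA = s(EA) x g(EA) - s(AC) x g(AC). All values of s and g are assumed. False-positive rates use 116 per arm throughout, as an approximation.

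| Removed EA / AC | Gap EA / AC | Bias | Share of 0.8 | False-positive rate |
|---|---|---|---|---|
| 20% / 20% | equal | 0 | 0 | 5% |
| 20% / 20% | 2.1 / 1.0 | 0.42 - 0.20 = 0.22 | 28% | 12.5% |
| 25% / 15% | 1.0 / 1.0 | 0.25 - 0.15 = 0.10 | 12.5% | 6.5% |
| 25% / 15% | 2.1 / 2.1 | 0.525 - 0.315 = 0.21 | 26% | 12% |
| 30% / 10% | 2.1 / 2.1 | 0.63 - 0.21 = 0.42 | 52.5% | 33% |

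More extreme assumptions give more, and swapping the arms reverses the sign. The documents give no removal shares by arm and no outcomes for removed women, so they cannot tell these rows apart.

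**6. Power if everyone is followed.** With 145 per arm the standard error is 2.1 x sqrt(2/145) = 0.247.

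- Difference 0.8: power 0.90.
- Difference 0.8 x 0.9 = 0.72 (assumed 10% dilution): 0.83.
- Difference 0.8 x 0.8 = 0.64 (the 20% who stop gain nothing): 0.74.
- For comparison, 116 completers per arm at 0.8: nominal 0.83, but no longer a comparison of the groups as randomised.

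**The case against.** The strongest reply is that the ITT set is defined on randomisation and one session, so removed women stay in it. The collapse towards PP needs two further assumptions: that leaving the study ends diary collection, and that missing values are not handled. The handling of missing values may be in an analysis plan that is not shown, and its absence here is not a finding. Follow-up after withdrawal might be described in a fuller protocol. This limits the claim but does not remove it. The rules say that women leave the study, and no analysis plan can recover diaries that were never collected.

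Further points stand:

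- A reader might infer that the removal rules match the PP exclusions exactly, or that the ITT analysis simply is a PP analysis. The table of grounds shows otherwise.
- A reader might infer that staff can remove women whom they expect to miss sessions. As worded, it is the patient who anticipates, which is close to self-withdrawal.
- The at-least-one-session condition could exclude women after the arm is known. However, Table 1 puts allocation and first treatment at the same visit, so few women should be affected.
- Both arms share the same needle points, retention time and 12-visit schedule, so attendance-driven loss may well be similar and the bias nil.
- The 20% allowance is not split by cause. Women who withdraw consent would be lost under any rule, so 58 is an upper figure for what the change could recover.

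**Conclusion.** The point holds in limited form and should be fixed. As written, the rules for leaving the study cover two of the PP conditions and end follow-up before the primary endpoint. The ITT set therefore lacks a post-baseline primary value for these women, and its observed data come close to the PP data.

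It would go too far to say that the estimate is biased or that randomisation is lost. The bias is of unknown size and direction, and zero when removal share times outcome gap is equal across arms. The range of 0.22 to 0.37 micturitions per day rests on assumed one-arm selection with correlation 0.3 to 0.5 and on the full 20% being removed in each arm. It shows what could happen, not what is expected. The conclusion also assumes that leaving the study means no further diary, which is the natural reading of the text.

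**What to change.** - **Dropout criteria; Prohibited and permitted concomitant treatment:** separate stopping trial treatment from leaving the study. When treatment stops remains a matter for the investigators, and no change to those rules is proposed. State that the week-6 and week-10 diary, OABSS and KHQ are sought from every randomised woman unless she withdraws consent, including women who anticipate missing sessions.
- **Statistical analysis:** define ITT as all randomised women in the arm allocated. For analysis purposes, let the 10-session and medication conditions act only through the PP set. The method for values still missing can be left to the analysis plan.
- **Abstract and Outcomes:** reconcile the two statements on participant blinding.

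The cost is a short amendment, feasible while the trial is, as Trial status puts it, still at the proposal stage, plus assessments for at most about 58 women. Some values will be recorded after other OAB treatment has started. The effect may be diluted: power with 145 per arm is about 0.90 with no dilution, 0.83 with 10% dilution and 0.74 if the 20% who stop gain nothing.

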### Randomization, allocation concealment and blinding

A table of random numbers will be produced according to sample size using the statistical software SAS (version 9.4; SAS Institute Inc., Cary, NC, USA), and sealed in opaque envelopes. The envelopes will be delivered to each research center and stored in a double-locked cabinet. The practitioner will open the corresponding envelope and allocate the participants who meet the eligibility criteria after signing an informed consent form. Participants will be randomly allocated to the electroacupuncture (EA) group or the acupuncture (AC) group at a ratio of 1:1. After the practitioner checks the group allocation for the subject, the envelope will be stored again in a separate, double-locked cabinet.

Randomization will be stratified by centers and is conducted with concealment of the randomization list.

Practitioners cannot be blinded, and they will be excluded from the assessment procedure. Outcomes will be assessed by researchers who are not involved in the intervention procedure.

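### Allocation concealment is weakened: the unblinded treating practitioner opens the envelope at the visit where the qualifying diary is first due, and a woman allocated but not yet needled leaves the ITT set

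*Protocol article*

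**What the plan says.** The section on randomization, allocation concealment and blinding sets out the procedure. A SAS-generated table is prepared "and sealed in opaque envelopes". Then: "The envelopes will be delivered to each research center and stored in a double-locked cabinet". Then: "The practitioner will open the corresponding envelope and allocate the participants who meet the eligibility criteria after signing an informed consent form". After the assignment is read, the envelope goes into a separate locked cabinet. The section adds: "Randomization will be stratified by centers and is conducted with concealment of the randomization list". On roles it says: "Practitioners cannot be blinded, and they will be excluded from the assessment procedure".

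Inclusion criterion 5 requires a mean of more than eight micturitions per day, plus an urgency rating above 2 and/or urgent incontinence, "on the 3-day bladder diary during a 1-week screening period".

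Table 1 marks the inclusion/exclusion check at visit 1 only. The row "Random allocation" is marked at visit 2, as is the first treatment session. The 3-day diary is marked at visits 2, 13 and 14, with no mark at visit 1.

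The Statistical analysis section limits the ITT set to women who were randomly allocated and received at least one session.

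**The concern.** Two stated features combine. The person who assigns is the person who treats and knows the arm, and the only separation of roles protects outcome assessment, not entry or assignment. In addition, the schedule does not place a completed eligibility decision before allocation, because the diary that decides criterion 5 first appears at the allocation visit.

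A seal protects decisions made before it is broken. It does not protect the interval between opening and the first needle. If eligibility is still being completed at that visit, a woman can be judged ineligible, or sent away, by someone who knows her arm, and the ITT definition then removes her. Exclusion of this kind can depend on the arm. ANCOVA on the baseline measurement corrects only for differences that baseline explains. If women are excluded according to expected response, the remaining difference stays in the treatment estimate.

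**Working it through.** The article states no figure on this point, so the main check compares its sections.

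**1. Who assigns.** By the randomization section, the practitioner opens the envelope and allocates. By the same section, that person cannot be blinded. By the Interventions section, the needling is done by licensed Korean medical doctors, and these are the practitioners in question.

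**2. When eligibility can be known.**

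| Item | Visit in Table 1 |
|---|---|
| Eligibility check | 1 |
| First 3-day diary | 2 |
| Random allocation | 2 |
| First session | 2 |

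Criterion 5 needs the diary from the screening week. Visit 1 is week 0 and visit 2 is in week 1, so a diary kept in that week is naturally handed in at visit 2. Two readings remain:

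- Eligibility is closed at visit 1, as Table 1 marks it. Criterion 5 is then ticked before its data are recorded.
- Eligibility is closed at visit 2. It is then completed at the allocation visit, and Table 1 shows no step for it.

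Neither reading matches the randomization section, under which only women who already meet the criteria are allocated, unless an unmarked confirmation takes place at visit 2.

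**3. How fine the decision is.** A 3-day mean above 8 needs more than 3 × 8 = 24 entries. A woman with 24 fails and one with 25 (25/3 = 8.33) passes, so a single diary entry can decide this part of the criterion. It matters who counts, and when.

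**4. What the analysis does with a late exclusion.** Envelope opened and session given: in the ITT set. Envelope opened and no session: out. The definition therefore allows removal after the assignment is known.

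**5. Sensitivity, on assumed values only.** Suppose a fraction f of one arm is affected by selection, and their expected change differs by d micturitions per 24 h beyond what baseline explains. Then bias = f × d. With the article's SD of 2.1 and 116 per group, SE = 2.1 × √(2/116) = 0.276. Two-sided type I error = Φ(bias/SE − 1.96) + Φ(−bias/SE − 1.96).

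| f | d | Bias | Type I error |
|---|---|---|---|
| 0.05 | 1 | 0.05 | 5.4% |
| 0.10 | 1 | 0.10 | 6.5% |
| 0.10 | 2 | 0.20 | 11.2% |
| 0.20 | 2 | 0.40 | 30.6% |

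The values of f and d are not in the documents, and a two-sided test is assumed. The last row is extreme and serves only to bound the table.

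**The case against.** The strongest reply is that the article does describe concealment. Envelopes are sealed and opaque, storage is double-locked, the list is concealed, and opening follows consent and eligibility. If that order is kept, nobody knows the next assignment when entry is decided, and sharing a visit does not in itself break concealment. This stands, and it is why the point is weakened concealment and not failed concealment.

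A reader might go further and infer that the practitioner picks an envelope from the stock, or could swap one for another. The text does not say so. It speaks of the corresponding envelope, which most naturally means one already tied to the participant. Nor does it say that the practitioner holds the key or judges eligibility. Foreknowledge of the next assignment would need a seal broken early or envelopes used out of order, and neither is in the written plan. The absence of sequential numbering, a log or a named keyholder proves nothing, because an article commonly leaves these to the full protocol.

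A reader might also want a headline number. For example, 10 of 145 women replaced by others one SD better gives 10/145 × 2.1 = 0.145 micturitions per 24 h, or 0.145/0.8 = 18% of the planned difference. The count of ten has no source. The 2.1 is the SD given for the change, not for what remains after baseline adjustment. The figure illustrates sensitivity and estimates nothing.

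Finally, the interval between opening and needling falls within one visit, which limits how many women could be lost in it. That is fair. What the objections leave untouched is the mismatch between Table 1 and criterion 5, the choice of an unblinded treating practitioner to open and allocate, and the ITT rule that lets a known assignment be followed by removal.

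**Conclusion.** The point holds in a limited form. Concealment is weakened because an unblinded treating practitioner opens site-held envelopes at the visit where the deciding diary is first due, while eligibility is ticked one visit earlier. The ITT definition adds to this by dropping women allocated but not treated.

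The conclusion rests on Table 1's columns as they appear in the text, and on the visit 2 diary mark being the diary that criterion 5 uses, since no earlier one is scheduled. The size of any bias cannot be estimated from the documents. The case for change is that the gap is plain and cheap to close, not that a bias of known size is expected.

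**What to change.** - **Schedule.** Reconcile Table 1 with criterion 5 by adding an eligibility confirmation at visit 2, after the diary is handed in and before allocation.
- **Roles.** Have the blinded assessor already on the trial, not the treating practitioner, calculate the diary mean and sign eligibility before the envelope is opened. The assessor does this without knowing the arm and stays blinded afterwards.
- **Analysis set.** Count every participant whose envelope is opened as randomised, and keep her in the ITT set whether or not a session follows. Amend the Statistical analysis section accordingly.

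The cost is a few minutes and one signature per participant at visit 2, with an assessor available at that visit. A woman kept in the ITT set without treatment may have no week 6 diary, so it should still be requested. If it is missing, she is handled like other missing primary outcomes. The Trial status section describes the trial as proposed, so on the article's own account the change can be made before enrolment.
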